# Jail-to-community treatment continuum for adults with co-occurring substance use and mental disorders: study protocol for a pilot randomized controlled trial

**DOI:** 10.1186/s13063-017-2088-z

**Published:** 2017-08-04

**Keywords:** Jail, Mental illness, Substance use, Open trial, Randomized controlled trial

## Abstract

**Background:**

Adults with co-occurring mental and substance use disorders (CODs) are overrepresented in jails. In-custody barriers to treatment, including a lack of evidence-based treatment options and the often short periods of incarceration, and limited communication between jails and community-based treatment agencies that can hinder immediate enrollment into community care once released have contributed to a cycle of limited treatment engagement, unaddressed criminogenic risks, and (re)arrest among this vulnerable and high-risk population. This paper describes a study that will develop research and communication protocols and adapt two evidence-based treatments, dual-diagnosis motivational interviewing (DDMI) and integrated group therapy (IGT), for delivery to adults with CODs across a jail-to-community treatment continuum.

**Methods/design:**

Adaptations to DDMI and IGT were guided by the Risk-Need-Responsivity model and the National Institute of Corrections’ implementation competencies; the development of the implementation framework and communication protocols were guided by the Evidence-Based Interagency Implementation Model for community corrections and the Inter-organizational Relationship model, respectively. Implementation and evaluation of the protocols and adapted interventions will occur via an open trial and a pilot randomized trial. The clinical intervention consists of two in-jail DDMI sessions and 12 in-community IGT sessions. Twelve adults with CODs and four clinicians will participate in the open trial to evaluate the acceptability and feasibility of, and fidelity to, the interventions and research and communication protocols. The pilot controlled trial will be conducted with 60 inmates who will be randomized to either DDMI-IGT or treatment as usual. A baseline assessment will be conducted in jail, and four community-based assessments will be conducted during a 6-month follow-up period. Implementation, clinical, public health, and treatment preference outcomes will be evaluated.

**Discussion:**

Findings have the potential to improve both jail- and community-based treatment services for adults with CODs as well as inform methods for conducting rigorous pilot implementation and evaluation research in correctional settings and as inmates re-enter the community. Findings will contribute to a growing area of work focused on interrupting the cycle of limited treatment engagement, unaddressed criminogenic risks, and (re)arrest among adults with CODs.

**Trial registration:**

ClinicalTrials.gov, NCT02214667. Registered on 10 August 2014.

**Electronic supplementary material:**

The online version of this article (doi:10.1186/s13063-017-2088-z) contains supplementary material, which is available to authorized users.

## Background

More than two million adults with serious mental illnesses (SMIs), including schizophrenia-spectrum, bipolar, or major depressive disorders, are admitted to US jails annually [1]. A majority of justice-involved adults with SMI also have alcohol or drug use problems. Substance use among adults with SMI is a complicating treatment factor, as drug and alcohol use worsens illness trajectories [2–4], increases the cost of treatment [5], and is associated with multiple negative outcomes, including homelessness, arrest, and violence [6–8]. However, there are many jail-based barriers to treatment for co-occurring mental and substance use disorders (CODs), including a lack of evidence-based treatment options and the often short periods of incarceration. There also is limited communication between jails and community-based treatment agencies, which decreases the likelihood of immediate entry into community care upon release. As a result, justice-involved adults with CODs experience high rates of treatment failure, and jail-based and community-based services struggle to intervene effectively. Together, these issues have contributed to a cycle of limited treatment engagement, unaddressed criminogenic risks, and (re)arrest among this vulnerable and high-risk population [9–11].

Although evidence-based programs for CODs are available for inpatient and outpatient settings [2, 5, 10, 12, 13], effective treatment programs for justice-involved adults with CODs are limited [4, 6, 14–16]. Despite an inmate’s constitutional right to adequate healthcare [17], behavioral health treatment in jail is rarely evidence-based or focused on key leverage points, such as community re-entry or criminogenic risks. Several factors have contributed to this lack of evidence-based care, including jails’ limited capacity to respond to inmates’ behavioral health needs, the long-standing mission of incapacitation and punishment rather than rehabilitation, and the often short periods of incarceration and frequently unknown release dates for inmates, which limits the opportunities for and duration of in-jail treatment when available. Also, frequent and ongoing coordination with community-based agencies regarding inmates’ immediate enrollment in community services upon release from jail remains a challenge [18].

The issues are as follows: (1) Can existing evidence-based practices be adapted and delivered to justice-involved adults with CODs across both jail and community settings in a way that mitigates these barriers while also reducing re-arrest, substance use, and psychiatric symptoms and improving quality of life? (2) Can communication protocols be developed that facilitate immediate entry into community-based services upon release from jail? If so, what are the available and effective interventions that are portable to the jail setting and amenable to the inclusion of criminogenic risks? In addition to existing guidelines and recommendations for jail-based services [18, 19], the mental health services literature describes several strategies that focus on organizational and clinical changes and the development of effective intra- and inter-agency communication that improves outcomes associated with transitions from institutional to community care [20–24]. These include discharge planning, information sharing, monitoring of clients post-release, immediate and intensive community-based care, and peer support workers who span both the institutional and community settings. Still, the development and adoption of and adherence to guidelines, recommendations, and improvement interventions for clinical care with justice-involved adults with CODs have proven difficult in both the jail setting and during the transition to the community.

### Objectives

The objectives of the current study are to (1) develop research protocols to obtain access to a jail population, implement a rigorous research design, including randomization to a pilot trial, and ensure that participants do not perceive any undue coercion to participate; (2) develop communication protocols so that jail and community treatment are coordinated and linked for effective community re-entry; and (3) adapt the clinical content of extant evidence-based programs to better address both behavioral health and criminogenic needs of jail inmates with CODs, including anger management, harm reduction, illness management, criminal thinking, antisocial peer networks, and treatment motivation. The following research aims were designed to address these objectives:
**Aim 1:** To adapt evidence-based interventions for delivery to jail inmates as they transition from institutional to community living, examining the initial acceptability of the adaptations through an uncontrolled open trial
**Aim 2:** To conduct a pilot randomized controlled trial (RCT) to establish knowledge in three priority areas:
*Aim 2.1*: The feasibility and acceptability of the adapted interventions
*Aim 2.2*: The feasibility and acceptability of the proposed research and communication protocols
*Aim 2.3*: The effectiveness of and estimated effect sizes associated with the adapted interventions vis-à-vis reductions in re-arrest, substance use, and psychiatric symptoms, and improvements in uptake of usual care.

## Methods/design

This project was developed in partnership with multiple community organizations, including the county’s managed care organization, multiple community-based provider agencies, and the county jail. Each of these partners helped shape the proposal, including the development of the communication and research protocols and the selection of the treatments to be adapted. The Standard Protocol Items: Recommendations for Interventional Trials (SPIRIT) checklist is included as Additional file 1, and the SPIRIT figure for the RCT is presented in Fig. 1. The study flowchart is provided in Fig. 2.

**Fig. 1 Fig1:**
[figure not shown]
Pilot RCT enrollment, interventions, and assessments according to SPIRIT guidelines

**Fig. 2 Fig2:**
[figure not shown]
Pilot RCT study flowchart

### Interventions

Dual-diagnosis motivational interviewing (DDMI) [25–27] and integrated group therapy (IGT) [28–31] are two integrated dual disorder treatment (IDDT) programs with strong evidence bases. IDDT programs are the “standard of evidence-based treatment” for adults with CODs ([32], p. 317). After a review of multiple IDDT and non-IDDT treatment programs, our partner agencies believed DDMI and IGT to be appropriate candidates for adaptation to justice-involved populations.

#### Dual-diagnosis motivational interviewing

DDMI is an adaptation of motivational interviewing [26] that incorporates an integrated framework and accommodates the cognitive impairments and disordered thinking associated with CODs. For example, DDMI includes simplified open-ended questions, refined reflective listening skills, and integration of psychiatric issues into personalized feedback and decision making. Given its portability and effectiveness in few sessions [27], DDMI was thought to fit particularly well within the context of brief, but intensive jail-based treatment prior to community re-entry. In the current study, DDMI sessions lasting approximately 60 minutes will be delivered one on one to inmates in the jail prior to their first court appearance. When possible, inmates will receive a second DDMI session before anticipated release from jail.

#### Integrated group therapy

IGT is an evidence-based practice that has been cited by the National Institutes of Health (NIH) as one of five examples of “promising behavioral therapies” for adults with CODs ([33], p. 3). IGT uses cognitive and behavioral strategies to address substance use, psychiatric symptoms, and medication nonadherence via a focus on (1) promoting abstinence from drugs, including alcohol; (2) promoting adherence to psychiatric medications; (3) teaching mood- and thought-monitoring skills; (4) teaching social skills; and (5) improving other aspects of life functioning [30]. Because cognitive-behavioral therapies like IGT are effective for treating adults with CODs [34, 35], including the reduction of antisocial behaviors [36, 37], our partners believed that community-based IGT also was an appropriate treatment to adapt for the jail-to-community treatment continuum. The goal is to have inmates, within 1 week of release from jail, enroll in IGT and participate in 12 90-minute IGT sessions with four to eight other inmates for 6 weeks. IGT sessions will be run with an open enrollment format [30] to facilitate a quick jail-to-community transition period and rapid engagement in community-based treatment [9].

### Conceptual frameworks

Our treatment adaptation and implementation and communication protocol frameworks are described next.

#### Treatment adaptation framework

Our treatment adaptation framework is guided by the Risk-Need-Responsivity (RNR) model [38, 39] and the National Institute of Corrections’ (NIC’s) implementation competencies [40]. Within RNR, the risk principle indicates that individuals at highest risk of future adverse outcomes should be identified and resources allocated accordingly. The need principle asserts that interventions should target criminogenic needs related directly to adverse outcomes for the individual offender. The responsivity principle affirms that strategies should be sensitive to identified risk and needs, while being delivered in a way that considers individual factors that can affect treatment outcomes (e.g., learning style). There are eight NIC implementation competencies that also informed our treatment adaptation process: assess risk and need, enhance motivation, target interventions, cognitive-behavioral skill training, positive reinforcement, increase ongoing support, measure processes and practices, and measurement feedback.

Through the integration of RNR principles and NIC competencies, DDMI will be adapted for in-jail use with a focus on motivating the inmate for community re-entry, continuity of care, and uptake of routine outpatient services. IGT will be adapted for more intensive, staged delivery of sessions that target criminogenic risk and needs, while continuing to enhance motivation for uptake of routine outpatient services.

#### Implementation framework

Our implementation framework is guided by the Evidence-Based Interagency Implementation Model (EB-IIM) for community corrections [40]. This framework considers multiple, interacting levels at which implementation must occur, including the role of inner and outer settings in implementation. For example, we will focus on developing knowledge and building a foundation through the open trial (i.e., preparation phase), in addition to establishing agreed-upon expectations for the jail and community partners and aligning the jail’s policies and procedures to accommodate changes identified through the two trials. Finally, ongoing treatment adaptations, informed via open trial results, should improve the likelihood of sustaining a successful jail-to-community-based treatment continuum through and then beyond the pilot RCT.

#### Communication framework

Our communication protocols will be based on the Inter-organizational Relationship (IR) model that emphasizes situational factors, as well as process, structural, and outcome dimensions in inter- and intra-agency communication. The IR model defines the situational factors (e.g., need for resources) and process (e.g., intensity of information flow), structural (e.g., complexity), and outcome dimensions (i.e., perceived effectiveness) necessary for inter-agency collaboration. Thus, in addition to developing and testing inter-agency communication protocols (e.g., from jail to community treatment), we also will develop and test intra-agency communication protocols (e.g., how to manage scheduling conflicts between IGT and usual care services). The IR model has been used effectively across service settings [41–44] and maps onto the technical, procedural, and resource dimensions of the EB-IIM’s foundation core [40].

### Study design

The study consists of two phases: (1) an uncontrolled open trial and (2) a pilot RCT. During the open trial phase, we will collect data to inform the refinement of the research and communication protocols and the adapted interventions—broadly, the jail-to-community treatment continuum. For example, results from the uncontrolled open trial may result in changes to the inmate participant recruitment and consent process, procedures for facilitating inter-agency communication, and additional adaptations to the DDMI-IGT continuum training materials, manuals, or session handouts. All modifications to the research and communication protocols and to the adapted interventions will be made in collaboration with community partners throughout the uncontrolled open trial and implemented in the pilot RCT.

### Setting

The study will be conducted at a large urban county jail in the southeastern USA. The jail’s average daily census ranges between approximately 1300 and 1450 with one-quarter of those inmates identified as being in need of mental health evaluation beyond standard screening completed during booking. Within 24–48 hours, on average, all inmates have their first court appearance. From there, inmates are either (1) bonded out or have their charges dropped or (2) detained and sent to Misdemeanor or Felony Court. From Misdemeanor or Felony Court, inmates are released or sentenced.

### Inmate participants

Inmate participants will be broadly representative of adults with CODs in a large urban county jail. Twelve inmates will be enrolled in the *open trial* and 60 in the pilot *RCT*. Eligibility criteria are: 18 to 65 years of age; incarcerated in the county jail; a resident of the county; able to speak and read English; and meet Diagnostic and Statistical Manual of Mental Disorders, 4th edition (DSM-IV) diagnostic criteria for (1) drug or alcohol abuse or dependence and (2) a serious mental illness, including major depressive disorder, depressive disorder not otherwise specified (NOS), bipolar disorder I, II, or NOS, schizophrenia-spectrum disorder, schizoaffective disorder, schizophreniform disorder, brief psychotic disorder, delusional disorder, or psychotic disorder NOS, based on review of clinical records and input from available informants, including jail-based clinicians.

### Community partner participants

Community partner participants will be clinicians working in local behavioral healthcare agencies who will provide the intervention to treatment participants. Clinicians (*n* = 4) from a local behavioral health agency will be recruited and trained to provide the treatment to participants. Two clinicians will provide DDMI treatment to participants in the jail prior to release into the community. Two clinicians will provide the IGT treatment to participants in the community after release from jail. To be eligible, clinician participants must be providing clinical services to jail inmates with co-occurring substance use and mental health disorders, at least 18 years of age, able to speak/read English, and able to provide informed consent.

### Clinician training

Prior to the start of the open trial, we will provide 1 day of training on IDDT principles, frameworks for treatment adaptation and implementation, and the DDMI and IGT programs to all study clinicians. We also will provide a second day of training separately for the DDMI and IGT clinicians, focusing on jail- and community setting-specific issues relevant to each of the interventions. Clinicians will receive a booster training during the open trial that will address modifications and refinements to DDMI and IGT and the communication protocols, as informed by open trial data. Clinicians will be retrained prior to the start of the pilot RCT and will receive another booster session midway through the RCT.

### Participant identification and recruitment

Participants will be identified for potential participation in the study through routine screening measures at booking, including the Brief Jail Mental Health Screen [45] and other jail-specific mental health and substance use screening protocols. The Jail Mental Health Liaison will identify participants who meet the study inclusion criteria, which were noted above, and the jail-based clinician will approach potential participants (after booking but before the first court appearance) to inquire about interest in study participation.

#### Uncontrolled open trial

Recruitment and participation in the open trial will occur in two cycles to allow for evaluation and modification of the DDMI-IGT treatment continuum, as necessary. In the first cycle, six inmates will participate. The adapted interventions and communication and research protocols will be modified as necessary, based on inmate and clinician feedback. After modifications, another six inmates will participate in the second open trial cycle.

#### Pilot randomized controlled trial

For the pilot RCT, all inmates who consent to participate will be randomly assigned to one of two conditions: the DDMI-IGT treatment group or the control group. After consent, participants will receive their group assignment. All inmates will be given a preassigned study ID, each associated with assignment to either the treatment or control group, as determined by a random number generator. Participants will be informed of their allocation to study condition by the research interviewer. Allocation is not concealed, as participants will be asked to provide feedback on their satisfaction with, and preferences for, treatment (see Table 1).

**Table 1 Tab1:** Uncontrolled open trial and pilot RCT measures and assessment schedule

					Assessment schedule					
Aim	Construct	Measure	Measure characteristics	Informant	OT	RCT				
						T0	T1	T2	T3	T4
1, 2.1, 2.2	Acceptability	Client Satisfaction Questionnaire-8 (CSQ-8) [49, 50]	8-item measure of satisfaction with DDMI-IGT treatment continuum	Inmates	X				X	
1, 2.1, 2.2	Acceptability	Narrative Evaluation of Intervention Interview (NEII) [51]	16-item interview for evaluating interventions	Inmates	X				X	
1, 2.1, 2.2	Acceptability, feasibility	Focus groups	Semi-structured groups about satisfaction with treatment continuum and protocols; implementation barriers, impact on jail and agencies	Community partners	X				X	
1	Fidelity	DDMI Adherence Form [52]	10-item measure of adherence and competence of DDMI sessions	Community partners	X					
1	Fidelity	IGT Adherence Form [28]	15-item measure of adherence and competence of IGT sessions	Community partners	X					
1, 2.1, 2.2	Feasibility	Exit interviews	Semi-structured interview of treatment success, barriers	Inmates	X				X	
1, 2.1, 2.2	Feasibility	Administrative records	Call logs; number of inter- and intra-agency contacts	Community partners	X				X	
1, 2.1, 2.2	Feasibility	Service Tracking Form	Treatment recruitment; sessions attended in jail, session attending in the community; graduation rates	Community partners	X				X	
2.3	Effectiveness: clinical	Addiction Severity Index (ASI) [53]	27-item measure of alcohol and substance use in prior 30 days, or since last assessment	Inmates		X	X	X	X	X
2.3	Effectiveness: clinical	Brief Psychiatric Rating Scale (BPRS) [71]	18-item measure of psychiatric symptom severity	Inmates		X	X	X	X	X
2.3	Effectiveness: clinical	Short Form Survey (SF-12) [72, 73]	12-item measure of health status and impairment	Inmates		X	X	X	X	X
2.3	Effectiveness: clinical	Epidemiological Catchment Area Interview [74]	14-item measure of self-reported service and medication use	Inmates		X	X	X	X	X
2.3	Effectiveness: clinical	Triarchic Psychopathy Measure [75]	20-item disinhibition scale of externalizing behaviors	Inmates		X				
2.3	Effectiveness: clinical	Heinrichs-Carpenter Quality of Life Scale, Plus [76]	31-item quality of life scale	Inmates		X	X	X	X	X
2.3	Effectiveness: public health	Criminal Justice Records	Electronic law enforcement records of arrest; jail tracking of criminal justice contacts	Community partners						X
2.3	Effectiveness: treatment preference	CODs treatment preferences [77, 78]	Visual analog ranking of preference for 8 aspects of treatment	Inmates					X	
—	Sample description	Demographic information	Diagnosis; age; race/ethnicity; sex	Community partners		X				

*OT* uncontrolled open trial, *RCT* randomized controlled trial, *T0* baseline assessment conducted in jail at treatment program enrollment, *T1* within 1 week of jail discharge, *T2* 3 weeks after jail discharge (mid-IGT treatment), *T3* 6 weeks after jail discharge (end of IGT treatment), *T4* 6 months after jail discharge

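### The protocol says allocation is not concealed, for a reason that supports only the absence of blinding; read literally, the trial has no allocation concealment

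*Protocol article*

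**What the plan says.** The protocol article describes assignment in the subsection on the pilot randomized controlled trial, under Participant identification and recruitment.

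- **Mechanism:** "All inmates will be given a preassigned study ID, each associated with assignment to either the treatment or control group", with the arm determined by a random number generator.
- **Timing for the participant:** "After consent, participants will receive their group assignment".
- **Who tells the participant:** "Participants will be informed of their allocation to study condition by the research interviewer".
- **Concealment:** "Allocation is not concealed, as participants will be asked to provide feedback on their satisfaction with, and preferences for, treatment".

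The steps before assignment involve other staff. Under Participant identification and recruitment, "The Jail Mental Health Liaison will identify participants who meet the study inclusion criteria", and "the jail-based clinician will approach potential participants (after booking but before the first court appearance) to inquire about interest in study participation". Under Inmate participants, the diagnostic criteria are judged "based on review of clinical records and input from available informants, including jail-based clinicians".

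Under Aim 2 of the analytic plan, the groups are to be compared at baseline to see whether randomization succeeded, and consenters are to be compared demographically with refusers.

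**The concern.** Concealment and blinding are different safeguards. Concealment means that nobody who decides on eligibility, approach or consent can know the next assignment before those decisions are made. Blinding means that the arm stays unknown afterwards. An open-label trial cannot blind its participants, but it can still conceal its sequence. The article states the absence of the first and justifies it with an argument about the second.

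This is a stated rule with a stated reason, so it is not a detail that an article may leave to the full protocol. If the rule is followed as written, a staff member who knew the arm of the next ID could approach one inmate and pass over another. Criminal justice contacts and re-arrest are the primary outcomes, and the article names criminal history and psychiatric severity among its possible moderators. Jail staff may be able to see such traits at the point of approach.

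The consequences would reach beyond this trial. Testing whether a rigorous randomized design can be run in a jail is part of the first objective, and the estimated effect sizes are meant to guide the choice of primary outcomes in later research.

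**Working it through.** **1. The stated reason against the stated rule.** Table 1 places the satisfaction questionnaire and the treatment-preference ranking at T3, six weeks after jail discharge. Collecting them requires that participants know their treatment by then. It does not require that anyone know an assignment before consent. The reason therefore supports non-blinding and has no bearing on concealment.

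**2. Whether the surrounding text supplies concealment.**

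| Statement | What it settles | What it leaves open |
|---|---|---|
| Assignment is received after consent | When the participant learns the arm | What staff know before consent |
| The research interviewer discloses the arm | Who tells the participant | Whether the interviewer or others see the list earlier |
| The liaison identifies and the clinician approaches | Roles are separate | Whether either can see the link from ID to arm |
| IDs are preassigned and tied to an arm | The sequence exists in advance | Who holds it, and whether IDs reveal the arm |

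Nothing here contradicts the literal statement that there is no concealment. Nothing shows that recruiters have the list either.

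**3. Whether the planned checks would detect selection.** An inmate who is never approached is not a refuser, so selective approach does not appear in the consenter/refuser comparison. Baseline comparisons with 60 participants cannot exclude selection on unmeasured traits.

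**4. The plan's own figure.** The Power analyses section gives 80% power for N = 60, α = 0.15 and 9% of variance explained. A noncentral F test with 1 numerator degree of freedom gives 0.806 if 0.09 is entered as f², and 0.835 if 0.09 is converted first (f² = 0.09/0.91 = 0.0989). The figure reproduces and does not depend on concealment.

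**5. Illustration of size.** Every risk, share and skipping rate below is an assumption; none comes from the document. No treatment effect is assumed.

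*Case A.* Half of eligible inmates are high risk (60% re-arrested) and half low risk (20%). Half of the high-risk inmates are skipped when the next ID is treatment.
- High-risk share in the treatment arm: 0.25/(0.25 + 0.50) = 0.333
- Re-arrest, treatment arm: 0.333 × 0.60 + 0.667 × 0.20 = 33.3%
- Re-arrest, control arm: 0.5 × 0.60 + 0.5 × 0.20 = 40.0%
- Difference: 6.7 points

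*Case B.* Risks are 50% and 30%, with 30% of high-risk inmates skipped.
- High-risk share in the treatment arm: 0.35/(0.35 + 0.50) = 0.412
- Re-arrest, treatment arm: 0.412 × 0.50 + 0.588 × 0.30 = 38.2%
- Re-arrest, control arm: 40.0%
- Difference: 1.8 points

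*Scale.* With 30 per arm (assumed, since the ratio is not stated) and 40% risk, the standard error of the difference is √(0.40 × 0.60 × 2/30) = 12.6 points. The two cases are then 6.7/12.6 = 0.53 and 1.8/12.6 = 0.14 standard errors.

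*False-positive rate.* Suppose selection left a prognostic imbalance of b standard deviations on a continuous outcome, with 30 per arm and a two-sided t test at 0.15 (noncentral t, 58 degrees of freedom, noncentrality b√(30/2)).

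| b | False-positive rate (nominal 0.15) |
|---|---|
| 0.1 | 0.18 |
| 0.2 | 0.26 |
| 0.3 | 0.39 |
| 0.5 | 0.68 |

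**The case against.** The strongest reply is that the sentence is a slip of terminology. It directly follows the statement that the interviewer tells participants their allocation, and its reason is about participants, so 'not blinded' is a natural reading. Participants learn their arm only after consent, and three different roles identify inmates, approach them and disclose the arm. A list of IDs linked to arms is compatible with full concealment if it is held elsewhere. The list holder and the release method may well stand in the full protocol or the SPIRIT checklist, which are not shown.

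Most of this stands. A reader might infer that the sponsor deliberately exposed the sequence, that recruiters can foresee the next arm, or that the approaching clinician has a stake in who is treated. The document supports none of these. It gives no recruiter access to the list, says nothing about the order in which IDs are issued, and attributes no such interest to the clinician. A reader might also extend the concern to attendance at the group sessions. Only the treatment arm is offered them, and attendance is judged against a fixed threshold, so there is no between-arm comparison to distort. The illustrated re-arrest shifts are also small against sampling error.

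What the reply does not remove is the sentence itself. If it is literal, the design lacks a basic safeguard. If it is a slip, the protocol misdescribes its own design, and readers assessing bias will take it at its word.

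**Conclusion.** The wording error is certain: the article denies concealment and supports the denial with an argument for not blinding. Read literally, no allocation concealment exists, although IDs are tied to arms in advance. Selection bias is conditional. It can enter only if staff who judge eligibility, approach inmates or seek consent can see the link from ID to arm, and the document does not say whether they can. If they can, the planned comparisons under Aim 2 cannot rule it out.

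The size cannot be derived from the document. The shifts of 1.8 to 6.7 points and the false-positive rates of 0.18 to 0.68 rest wholly on assumed inputs, and they show the direction and possible scale only. The point calls for correction on either reading of the sentence, because recruitment to the randomized trial was still ongoing according to Trial status.

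**What to change.** Replace the sentence with:

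> Upcoming assignments are concealed from staff who identify, approach or consent inmates until eligibility is confirmed and consent is given; participants and clinicians are not blinded afterwards.

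For all remaining recruitment:

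- have the list linking IDs to arms held by someone not involved in recruitment;
- issue study IDs that do not reveal the arm;
- release each assignment only after consent, by sealed opaque envelope or electronic release.

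If earlier enrolments were unconcealed, record the date of the change and report a before/after sensitivity analysis, which will be imprecise with 60 participants in total. If concealment already operates, it is enough to correct the wording and say so.

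Permuted blocks are not needed for this purpose; at a single unblinded site they can make assignments late in a block easier to guess. Release need not wait for the baseline assessment, which matters because the first court appearance comes within 24–48 hours on average. The cost is a small administrative step at each enrolment, with no additional participants.
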